### Intervention

The description of the intervention follows the TIDieR checklist and guide [72].

#### Name and Rationale

The intervention is called Just in TIME and addresses the importance of early intervention for this target group. The word “TIME” stands for “Try, Identify, Move, and Enjoy,” which also characterizes the key aspects of the intervention, which aims to decrease FAPDs among 9- to 13-year-old girls through dance and yoga. Essential elements of the intervention included a focus on enjoyment, socialization, and playful creativity in an undemanding environment. We chose a combination of dance and yoga because of experiences from an earlier study [38] that targeted adolescent girls with internalizing problems and evaluated a dance intervention. The study participants appreciated the intervention and rated it to be a positive experience [38], but at the end of the intervention period, they started to request yoga as an add-on at the end of the sessions. They believed that it would be a valuable closure to the session to help them tune in to the relaxation. These requests were a form of evaluation that the research team took into account when designing the current study.

#### Materials

Informational material was distributed during the training of the intervention providers. It consisted of written course materials and visually recorded practical choreography and sequences, all provided by the intervention coordinator.

#### Procedures

The intervention was performed as a group activity twice a week after school hours during an 8-month period. The duration of the class was 60 minutes, comprising 30 minutes of dance practice, 25 minutes of yoga including relaxation, and 5 minutes of short reflection (Table 1). Throughout the intervention period, the participants were encouraged to practice their favorite dances, yoga poses, or relaxation techniques at home if they wanted to. Both centers followed the same routine.

**Table 1 table1:** The 60-minute Just in TIME dance and yoga class.

Minutes	Section	Description
10	Dance: warm-up	The warm-up section aimed to get the participating girls to be active and take part in the social cohesion. It included up-tempo music with prominent drum beats and captivating rhythm. Expansive, easy, accessible movements activated large muscle groups.
20	Dance	The dance choreography section included mostly structured dance as a group under the guidance of an instructor but also included improvisation and playful exploration of movement. The focus was on enjoyment and socialization rather than performance. The intention was to offer an opportunity to experience one’s own body in a positive way with popular music in an undemanding and supportive atmosphere as well as to increase heart rate with moderate-to-vigorous physical activity. Month 1-2: Focus on experiencing joy of movement, feeling safe, and getting to know each other. Dance style: show jazz. Month 3: Focus on expansive movements, “claiming space,” determination, and integrity. Dance style: show jazz and street dance. Month 4: Focus on body awareness, slow movements, and grace. Dance style: jazz and contemporary dance. Month 5-6: Focus on increasing energy and working together as a group in the choreography. Dance style: show jazz. Month 7-8: Focus on enjoyment and meeting variations in the dance movements (high-low, firm-soft, and expansive-small variations). Dance style: show jazz and floor work.
20	Yoga	The yoga section focused on playful movements, such as creative yoga storytelling combined with asanas (body poses), a focus on breathing, and attention. Asanas were performed individually or in pairs and, when appropriate, together as a group. Month 1-2: *balasana* (child’s pose), *marjaryasana* (cat pose) and *bitilasana* (cow pose), *parsva sukhasana* (seated side bend pose), *uttanasana* (standing forward bend), *upavistha bitilasana marjaryasana* (seated cat-cow pose), *jathara parivrtti* (revolved abdomen twist pose) Month 3: *parivritta sukhasana* (sitting twist pose), *parsvaparvatasana in tadasana* (standing side bend), *uttanasana* (standing forward bend), *sufi grind* (seated torso circles), *paranamuktasana* (knees to chest), *jathara parivrtti* (revolved abdomen twist pose) Month 4: *virabhadrasana* II (warrior II), *ardha chandrasana* (half-moon pose), *ardha setubandhasana* (half-bridge pose), *adho mukha sukhasana* (easy pose forward bend), *upavistha bitilasana marjaryasana* (seated cat-cow pose), *jathara parivrtti* (revolved abdomen twist pose) Month 5-6: *vrksasana* (tree pose), *utthita trikonasana* (extended triangle pose), *upavista konasana* (seated wide angle posture), *adhomukha svanasana* (downward-facing dog posture), *balasana* (child’s pose), *paranamuktasana* (knees to chest), *sufi grind* (seated torso circles), *jathara parivrtti* (revolved abdomen twist pose) Month 7-8: extended focus on creative yoga storytelling in group, *phalakasana* (plank pose), *adhomukha svanasana* (downward-facing dog posture), *bhujangasana* (cobra pose), *ardha setubandhasana* (half-bridge pose), *jathara parivrtti* (revolved abdomen twist pose)
5	Relaxation	*Pranayama* (slow deep breathing and attention to the breath), *savasana* (corpse pose), guided relaxation to increase calmness, and lying down with blankets. During the relaxation, a brief massage on the shoulders was offered by the instructors (voluntary).
5	Reflection	Finally, a short voluntary sharing session was held while seated in a circle, highlighting a positive experience during this particular class.

#### Intervention Providers

Each group included 7 to 14 girls and was under the guidance of 2 instructors, one at a time. The instructors had a profession in either health care or pedagogy, had experience working with young people, and were educated in teaching children or adolescents in dance (instructor training) and yoga (ie, registered yoga teacher 200-hour training). Prior to the start of the intervention, all instructors attended a 2-day course administered by the research team. This course consisted of practical instructions from the intervention coordinator about the dance and yoga session according to the standardized program design, including dance choreographies and yoga sequences adjusted to the target group as well as teaching style (nonjudgmental and supporting approach). Lectures about theories and underlying mechanisms and about guidelines and ethical aspects regarding children with FAPDs were also given.

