### Study Design

This study, called Just in TIME (Try, Identify, Move, and Enjoy), started in 2016 when the first intake was performed and will end in 2023. The study is a prospective randomized controlled trial with 2 parallel groups—an intervention group and a control group—of girls aged 9 to 13 years with functional abdominal pain, IBS, or both. The intervention consists of dance and yoga sessions 2 times a week for 8 months. The control group receives standard care as school health care or primary care. The outcomes are measured at baseline and after 4, 8, 12, and 24 months. A long-term follow-up will be performed 5 years from baseline (Figure 1). At all follow-ups, data are collected for both the intervention and control groups. The trial is being conducted in 2 cities in Sweden.

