#### Randomization

When the baseline measurement was completed and the eligibility check was accomplished, the sample was randomized into an intervention group and a control group. Randomization was performed by an external statistician using minimization based on pain intensity and age at baseline [78].

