### Analyses

#### Statistical Analysis

The Just in TIME study follows the intention-to-treat paradigm. Complementary analyses will be performed per protocol and according to the number of sessions the participant attends.

For baseline statistics between the groups, descriptions will be constructed using frequencies and proportions for categorical data and means and standard deviations for continuous variables. Baseline characteristics will be compared using the Fisher exact test for dichotomous outcomes, the Mantel-Haenszel chi-square test for ordered categorical outcomes, and the Mann-Whitney U test or unpaired *t* test for continuous outcomes. A *P* value of <.05 for the 2-tailed test will be considered statistically significant for all outcomes. When deemed necessary, correction for multiple significance will be performed.

The primary outcome analysis will initially be performed using a Fisher exact test to evaluate differences between groups. To analyze the change in scores from baseline between groups for approximately normally distributed variables, a repeated-measures covariance pattern mixed model will be used, adjusting for significant differences at baseline. To identify predictive factors at baseline that might be associated with the primary outcome, a univariable logistic regression analysis followed by a stepwise multiple logistic regression analysis will be performed.

The distribution of continuous variables will be described using the mean and standard deviation or median and interquartile range. Categorical variables will be described with numbers and percentages.

Study participants who choose to leave the intervention before the study is finished are encouraged to complete all assessments. Missing data will be handled with multiple imputations or within the mixed model.

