## Discussion

Considering that FAPDs are prevalent among young girls, cost-effective and easily accessible interventions are warranted to reduce the negative consequences arising from these disorders. Physical activity is an effective strategy, but intervention studies are needed to better understand what types of activities facilitate regular participation for this target group. This study will provide new insights regarding the effectiveness of dance and yoga as an active and health-strengthening intervention for girls aged 9 to 13 years with FAPDs. To our knowledge, this is the first study to investigate the influence of these activities combined in an after-school setting.

Worth mentioning is that the current study cannot determine whether one part of the intervention had a greater effect than another. The aim was to evaluate the combination of dance and yoga and the effect of the entire intervention. The supportive group setting, the instructors, the music, or specific parts of the intervention may influence the health effects in different ways. Additionally, it is possible that behavior change alone (ie, engaging in a new organized activity) could contribute to changes in abdominal pain. As always, when testing complex interventions, there are many factors that can affect the outcomes. However, this is also the fact in clinical and real-life situations, and we have chosen a randomized design to account for confounding factors as much as possible.

Methodological strengths of the study include the randomized controlled design, the preregistration in a clinical trials registry, the long follow-up, and the combination of quantitative and qualitative measures. We also verified the FAPD diagnosis with an examination and laboratory evaluation performed by experienced physicians before including the participants in the study.

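### Only the intervention arm is taught in classes, and no analysis described in the article has a class term; if outcomes correlate within class, P values and intervals are too optimistic

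*Protocol article*

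**What the plan says.** Allocation is individual. The Randomization section states: "Randomization was performed by an external statistician using minimization based on pain intensity and age at baseline".

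Delivery differs between the arms. Under Procedures: "The intervention was performed as a group activity twice a week after school hours during an 8-month period". Under Intervention Providers: "Each group included 7 to 14 girls and was under the guidance of 2 instructors, one at a time". For the comparator, Study Design says: "The control group receives standard care as school health care or primary care".

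The Discussion names a route by which girls in one class could come to resemble each other: "The supportive group setting, the instructors, the music, or specific parts of the intervention may influence the health effects in different ways".

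The Statistical Analysis section fixes the primary test: "The primary outcome analysis will initially be performed using a Fisher exact test to evaluate differences between groups". For change scores it says "a repeated-measures covariance pattern mixed model will be used, adjusting for significant differences at baseline". For predictors of the primary outcome it says "a univariable logistic regression analysis followed by a stepwise multiple logistic regression analysis will be performed". None of these descriptions mentions class or instructor.

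**The concern.** This is a partially nested design: individual randomization, with clustering created by treatment in one arm only. Girls in a class share peers and instructors for eight months, and controls have no counterpart to that.

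Fisher's test has no place for a class term. A covariance pattern over visits models the correlation between one girl's own measurements, not the correlation between two girls in the same class. The logistic regression, as described, also treats girls as independent.

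Any positive within-class correlation makes the intervention-arm estimate less precise than these methods assume. The error runs in one direction: intervals too narrow and P values too small, for primary and secondary outcomes alike. Fisher's test reports no standard error, so there the fault would appear only in the P value.

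**Working it through.** **Inputs from the article.** Class size 7 to 14 (Intervention Providers). 64 intervention and 57 control girls allocated (Results). Expected proportions 30% and 10%, power 80%, 20% dropout, 75 per arm (Sample Size). Two-sided 5% level (Statistical Analysis). The ICC and the number of classes are not given; the ICCs below are assumptions.

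**1. The plan's own sample size.** With pooled variance under the null,

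n = [1.96·√(2·0.20·0.80) + 0.842·√(0.30·0.70 + 0.10·0.90)]² / 0.20² = (1.109 + 0.461)² / 0.04 ≈ 61.6, so 62 per arm.

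62 × 1.2 = 74.4, so 75 per arm and N = 150, as stated. The unpooled form gives 59 per arm; 59/0.8 = 73.75, so 74 per arm and N = 148. Both routes use a design effect of 1, so the sample size also assumes independent girls.

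**2. Number of classes.** 64/14 = 4.6 and 64/7 = 9.1, so about 5 to 9 classes. Mean class size m is 64/5 = 12.8 or 64/9 = 7.1.

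**3. Comparison of means.** The intervention-arm design effect is d = 1 + (m − 1)·ICC. The true standard error of the difference exceeds the naive one by r = √[(d/64 + 1/57) / (1/64 + 1/57)], and the true size of a nominal 5% test is about 2[1 − Φ(1.96/r)].

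Example with 5 classes and ICC .05: d = 1 + 11.8 × 0.05 = 1.59; r = √(0.04239/0.03317) = 1.13; 1.96/1.13 = 1.73; size about 8.3%.

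**4. Fisher's test.** Size was computed by enumerating all 64 v 57 tables, with beta-binomial classes in the intervention arm, independent controls, the ICC on the binary scale and a common event rate of 10% to 40%.

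| ICC | Means, 9 classes | Means, 5 classes | Fisher, 9 classes | Fisher, 5 classes |
|---|---|---|---|---|
| 0 | 5.0% | 5.0% | 3.4–4.1% | 3.4–4.1% |
| .01 | 5.3% | 5.6% | 3.7–4.4% | 3.9–4.7% |
| .02 | 5.7% | 6.3% | 4.0–4.7% | 4.5–5.3% |
| .05 | 6.7% | 8.3% | 4.8–5.6% | 6.2–7.1% |
| .10 | 8.4% | 11.6% | 6.3–7.2% | 9.1–10.3% |

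Simulated t tests with 5 classes (20,000 runs) agree: 8.2% at ICC .05 and 11.4% at .10.

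**5. What it does to an interval.** Take the planned 30% v 10% with 64 and 57 girls. The naive SE is √(0.21/64 + 0.09/57) = 0.070, so the interval is 20 ± 13.7 percentage points. With d = 1.59 the SE is √(1.59 × 0.21/64 + 0.09/57) = 0.082, so it is 20 ± 16.2 points.

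**The case against.** The strongest reply is that the size of the problem rests on an unknown. A reader might infer that the standard errors are too small and that type I error exceeds 5% as a matter of fact. The article does not support that: it gives no ICC, and at .02 or less the conservatism of Fisher's test keeps the primary analysis at about the nominal level. The standardized instructor course and booster sessions may also reduce differences between instructors, though not effects among peers. The sizes above refer to no average difference with classes varying around it. If the classes changed nothing for any girl, treatment would induce no class correlation at all.

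A reader might also infer that every analysis ignores clustering. The text fixes that for Fisher's test only. For the mixed model it is a reading of one sentence, and random effects are the kind of detail that an unseen analysis plan may hold. The article also calls Fisher's test the initial analysis, which leaves room for another.

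A third tempting step is to count city and wave as part of the one-arm clustering. Controls come from the same cities and waves, so those influences are common to both arms. Only class and instructors belong to one arm.

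Lastly, 5 to 9 classes estimate a class variance poorly, and often at zero. That is a fair warning against relying on a random effect alone. It is no reason to set the ICC to zero by default.

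What stands is the structure: the article describes one-arm classes, suggests how correlation could arise, and names a primary test that cannot allow for it.

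**Conclusion.** The point holds in conditional form. If outcomes correlate within class, the analyses as described give P values and intervals that are too optimistic. Over assumed ICCs of .01 to .10 and 5 to 9 classes, a comparison of means has a true size of about 5% to just over 11%, and Fisher's test about 4% to 10%. At ICC .05 these are about 7% to 8% and 5% to 7%. At .02 or less the primary test is at about 5% or below, while comparisons of means run slightly over.

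The figures rest on the allocated 64 and 57 girls, near-equal class sizes and, for Fisher's test, an ICC on the binary scale. This should be fixed, but it does not by itself invalidate the primary test.

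**What to change.** - **Mixed models:** add a random class effect in the intervention arm only, with each control girl as her own unit and no class variance in controls. Use Satterthwaite or Kenward-Roger degrees of freedom.
- **Primary outcome:** keep Fisher's test as the initial test. Accompany it with an analysis that allows for class and has a small-sample correction, for example cluster-robust standard errors with controls as singletons.
- **Sensitivity analysis:** report the between-arm difference with the intervention-arm variance multiplied by 1 + (m − 1)·ICC, for fixed ICCs from .01 to .10. This does not depend on a poorly estimated class variance.
- **Reporting:** give the number and sizes of classes, and the estimated ICC with its interval and its scale (binary or latent).
- **City and wave:** treat them as factors common to both arms, not as part of the class effect.

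The cost is analysis wording plus class membership, which should be recoverable because instructors recorded attendance. No new data are needed. The downside is somewhat wider intervals and an imprecise ICC.

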#### Modes of Delivery

Various styles of dance with a focus on enjoyment were performed during the intervention period. The yoga practice consisted of both playful movements (such as creative yoga storytelling) and calm physical postures with a focus on breathing and attention, which were performed individually, in pairs, and as a group. The intervention (further described in Table 1) was developed by the intervention coordinator (author AD). To ensure standardization in program delivery across both centers and between instructors over time, booster sessions were given 3 times during the intervention period (in addition to the initial 2-day course). The participants in the intervention were advised to wear practical soft clothes suitable for the activity, and no special shoes were needed.

#### Locations

The intervention took place in studios located in the center of Örebro and Västerås, Sweden, which were easily accessible by bus or walking. The studios had yoga mats and music equipment.

#### Frequency and Duration

The 8-month period was chosen because it corresponded to 2 school semesters. No classes were held during holidays; thus, 50 dance classes were held over 25 weeks. The practice can be classified as moderate-to-vigorous physical activity.

#### Tailoring and Modification

To address modifications, both dance and yoga movements were introduced in steps to include all participants regardless of previous experience. Alternatives were given when needed. No changes were made in the intervention.

#### Adherence

Adherence to the dance and yoga intervention was noted by the instructors. A strategy to maintain and improve fidelity was to consciously focus on relatedness and provide a feeling of social inclusion, supportiveness, and the chance to meet new friends. To keep the dance and yoga sessions interesting over the time period, a variety of styles and themes were presented, all distributed by the intervention coordinator. The intervention was delivered as planned throughout the 3 intervention years.

### Outcomes

This study includes biochemical and physiological measures, questionnaires (for the girls in the study and their legal guardians who answer questions about their daughters as a proxy), and qualitative interviews (with both the girls in the study and their legal guardians) (Figure 2). The questionnaire sessions are performed at the research centers, and the project team provides assistance. To retain as many participants as possible, reminder mail and emails are sent to participants. Notes about participants who discontinue or deviate from the study are made.

**Figure 2 figure2:**
[figure not shown]
Enrollment, interventions, and assessments. An “X” represents a child report and an “O” represents a legal guardian report. The PACES, enjoyment rating scale, and experiences questions were only asked to the girls in the intervention group. BSC: Bristol stool chart; ChilD-S: Children’s Depression Screener; CSSI-24: Children’s Somatic Symptoms Inventory-24; EQ-VAS: EuroQol visual analog scale; FPS-r: faces pain scale-revised; LH-YP: Life and Health – Young People; PACES: Physical Activity Enjoyment Scale.

#### Primary Outcome Measure

The primary outcome is the proportion of girls in each group who have reduced maximal pain, measured immediately after the intervention (8-month follow-up) with the FPS-r [76,77] in a pain diary in which the girls register their abdominal pain 3 times a day for 1 week. The psychometric features for the FPS-r are reported to be good [77].

#### Secondary Outcome Measures

##### Abdominal Pain and Gastrointestinal Issues

Abdominal pain is measured with the pain diaries with the FPS-r [76,77].

Abdominal pain is also measured in the questionnaires with a subscale in the Children’s Somatic Symptoms Inventory-24 (CSSI-24) (formerly known as the Children’s Somatization Inventory) [81-84]. The CSSI-24 is a valid and reliable instrument that assesses a variety of nonspecific somatic symptoms [81].

Pain drawings are used to elicit information about the location of pain symptoms [85,86]. A growing body of evidence supports pain drawings as an assessment of pain among children [85].

Fecal samples were collected at baseline and at 8 months for measurement of the intestinal bacterial composition. This is an important background variable that can affect how effective the intervention is for a participant and thus has prognostic significance for the treatment outcome [87].

The Bristol stool chart (BSC) is a well-recognized tool designed to classify the form and consistency of feces into 7 categories [88]. It is used in both clinical and experimental fields [89] and has been used to assess the intestinal transit rate. Normal stool consistency is considered type 3 to type 5 on the BSC [90].

